#### **2.2.4 Trial procedures, statistical considerations, and data management**

**Randomization, allocation concealment and blinding:** After informed consent and baseline assessment, participants will be randomly assigned to NICU-MT or standard care using a computer-generated randomization list, with ratio 1:1, in blocks with sizes of 2 or 4 varying randomly, using email and an online system. The random allocation sequence will be generated and administered by people with no involvement in the clinical work to ensure allocation concealment. One day before discharge to home, participants will be randomized a second time to post-discharge MT or standard care in a 1:1 ratio, using the same procedures. This two-step randomization was chosen as the best way to create balance among those remaining in the study for the aftercare phase, and to avoid differential drop-out in the NICU phase due to expectations for the aftercare phase. In multiple pregnancies, only the first-born infant will be included and randomized, while remaining siblings will receive the same interventions for ethical and practical reasons. Blinding of interventions is not possible, but all outcomes that are not self-reports will be blinded, and success of blinding will be tested.

**Power calculation and sample size:** No previous RCT examined effects of MT on the PBQ; two small RCTs included in our systematic review [25] and a recent non-randomized study [29] examined mother-infant bonding, but provided insufficient data for meta-analysis. Studies using the PBQ with other interventions found effects ranging from around 0.25 ([44], posttest) through 0.5 ([45], mothers at 1/6 months), 1.4 ([46], 4 months), 2 ([45], fathers at 1/6 months), 9 ([44], 3 months), with SDs ranging from 4 to 12. Assuming a difference of 4 points on the PBQ ( $SD = 8$ ) as a minimal clinically important difference for this study, power of 80% will be achieved for each main effect (each tested on a two-sided 2.5% significance level, i.e. 5% with Bonferroni correction for two tests) with a sample size of 155. Taking into account some clustering by country (ICC 0.01; 5 countries), this is increased to 203. To allow for 20% attrition, we will aim to include 250 infants (50 in each country) and their parents. This sample size will also ensure power for testing proportion differences of about 15% (e.g. binary analysis of problematic bonding; re-hospitalization). Special considerations are needed for multiple pregnancies (twins, triplets, etc.), which account for about 2% in Hordaland [4], but are more common in NICUs due to their elevated risk of preterm birth. Including all siblings would serve to increase the sample size, but may lower the resulting power due to cluster effects.

Therefore, we will only formally enroll and analyze the first-born sibling of each multiple pregnancy, although all will receive the intervention.

**Data analyses:** All randomized participants will be included in the main analysis (intention-to-treat). Descriptive statistics will characterize basic properties of the sample and provide information for power calculation for the multi-center study. Effects will be examined by testing the randomized groups for differences in the primary endpoint (t-test or Mann-Whitney; change in PBQ scores to 6 months CA), as well as by fitting linear mixed models. In the first modeling step we will assess the effect of the first randomization (Fig. 1) using the following model:

$$PBQ_{it} = \beta_0 + \beta_1 time_t + \beta_2 gr_i + \beta_{12} time_t gr_i + U_i + \varepsilon_{it} ,$$

where  $PBQ_{it}$  denotes the PBQ score for participant  $i$  at measurement  $t$ ,  $time_t$  the time from baseline at measurement  $t$  and  $gr_i$  the randomization group of participant  $i$ .  $\beta_0$ ,  $\beta_1$ ,  $\beta_2$  and  $\beta_{12}$  are the coefficients estimated in the model,  $U_i$  is an individual random term per participant and  $\varepsilon_{it}$  an independent, identically distributed error term. In the second step we refine the model to take into account both randomization steps, leading to the extended model:

$$PBQ_{it} = \beta_0 + \beta_1 time_t + \beta_2 grR1_i + \beta_{12} time_t grR1_i + \beta_3 grR2_i + \beta_{13} time_t grR2_i + U + \varepsilon_{it} ,$$

with the same notation as above and  $grR1_i$  and  $grR2_i$  denoting the groups from the first and second randomization, respectively. In these models  $\beta_1$  describes a group-independent time effect,  $\beta_2$  and  $\beta_3$  a time-independent group effect, and  $\beta_{12}$  and  $\beta_{13}$  the time-dependent change of the group effect. We will investigate both linear and simple contrasts (comparing each time point with the baseline) in time to assess the treatment effect. The same analyses will be done for the secondary outcomes; using an analogous generalized linear mixed model for binary outcomes. Per-protocol analyses will include those who received at least 6 MT sessions in the NICU and at least 5 MT sessions post-discharge, respectively; these are considered the minimum numbers for the intervention to be successful. Additionally, we will conduct exploratory statistical analyses for prespecified subgroups (sex; GA at birth [ $<28$  wks, 28 to  $<32$  wks, 32 to  $<35$  wks]; hearing status at discharge [normal vs. abnormal]; bonding at baseline [PBQ impaired bonding score  $\geq 11$  vs.  $<11$ ]) as well as qualitative/mixed-methods analyses of process data to maximize learning.

**Data management plan:** To promote transparency and applicability of trial results and to facilitate re-analysis by other researchers while also protecting anonymity, de-identified individual patient data will be made available through the Norwegian Centre for Research Data (NSD).

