**From 36 weeks PMA – Engagement in musical exchange:** This phase applies when the infant demonstrates readiness to engage in more interactive levels of musical exchange. Caregivers interact musically with the infant, using vocal inflection and sung cues to encourage the infant to achieve a quiet, alert state and engage in eye contact, vocalization, and rudimentary social interaction. Depending upon infant readiness, caregivers may use premature infant-friendly, basic musical toys to promote auditory localization, auditory tracking, visual tracking, eye contact, reaching, grasping, and mouthing. The therapist will encourage the caregiver to use preferred lullabies and children’s songs or to modify songs of kin [21] in order to encourage musical dialogue with the infant.

**Standard care during NICU:** This will vary across countries, but will typically include necessary medical care and a limited amount of interventions to reduce stress among infants and to inform and promote safety in parents [31].

**MT post-discharge from hospital:** Individual MT sessions will be offered, minimum 5 and maximum 7, 45-minute sessions per infant/parent distributed across six months. These will occur at municipal child health centers or at home, and comprise: (1) Verbal greeting and brief discussion of infant’s progress (approx. 5 min). (2) Musical greeting of infant and caregiver, encouraging caregiver to participate (5 min). (3) Engagement in musical exchange following the procedures described in the “from 36 weeks” category above, with therapist modelling musical engagement (approx. 10 min). (4) Discussion of current infant/parent challenges and strategies for using musical interactions to address these needs, with therapist modelling musical techniques to promote self-regulation or to facilitate musical interaction, depending upon needs identified by the caregiver (approx. 10 min). (5) Caregiver demonstration of techniques discussed during session (approx. 10 min). (6) Musical closure and reminder of planned timing for next visit (approx. 5 min). Any siblings may be involved if desired by the caregiver. Subsequent sessions will follow a similar sequence, adjusted to infant developmental level and ongoing needs. The therapist will work in close dialogue with those providing standard aftercare procedures.

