### 2.2.3 Outcomes

Outcomes will be assessed at several time points: at baseline; one to two days before discharge to home; at 6 months corrected age (end of MT; primary endpoint); and 12 months of corrected age (CA; chronological age reduced by number of weeks born preterm [30]). Data collectors and assessors will be trained in assessment procedures and blinded to participant allocation; success of blinding will be verified.

**Primary outcome: Bond between primary caregiver and infant** will be evaluated at all time points (**primary time point: 6 months CA**) using the Postpartum Bonding Questionnaire (PBQ). PBQ is a self-rating screening instrument for disorders of the early mother-infant relationship consisting of 25 statements on a six-point Likert scale (each 0-5; sum score ranging from 0 to 125; high = problematic), addressing problems in the mother-infant relationship based on weakened bonding; rejection and anger; anxiety about care; and risk of abuse [32]. The scale is validated and widely used in clinical practice and research [33]. It has been translated and tested in several languages and cultures [34] and has high internal consistency [35] and test-retest reliability [32], also in the Norwegian version [36].

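### The plan names no stratification for either randomization and does not say whether lists are central or per site; either reading leaves a modest, cheaply fixed weakness, and country is missing from the analysis.

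*Combined protocol and SAP*

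**What the plan says.** Section 2.2.4 (Randomization, allocation concealment and blinding) assigns participants to standard care or NICU music therapy "using a computer-generated randomization list, with ratio 1:1, in blocks with sizes of 2 or 4 varying randomly, using email and an online system". One day before discharge, "participants will be randomized a second time to post-discharge MT or standard care in a 1:1 ratio, using the same procedures". The sequence is "generated and administered by people with no involvement in the clinical work to ensure allocation concealment". The same paragraph concedes that "Blinding of interventions is not possible".

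No section names a stratification factor, gives the share of blocks of each size, or says whether there is one central list or one per country or site.

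On country, section 2.2.2 says of standard NICU care: "This will vary across countries". The sample-size paragraph raises N from 155 to 203 for clustering in five countries (ICC 0.01), then to 250 for attrition. The data-analysis paragraph offers a t-test or Mann-Whitney test and two linear mixed models. The only random term is per participant, and there is no country term. The second (extended) model contains both randomization factors.

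**The concern.** The plan expects countries to differ, yet country appears neither in the described randomization nor in the analysis. The two-step scheme is justified as a way to create balance among those who remain for aftercare, yet nothing described balances the second allocation within the first arms. That crossing is what a 2x2 design depends on.

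Blocks of 2 and 4 are also small for a trial in which staff and parents see every allocation. The primary outcome is a caregiver report ("PBQ is a self-rating screening instrument"), and medical staff judge when an infant is stable enough to enter. Someone who can infer the next arm could influence who is enrolled, and when. Keeping the list away from clinical staff does not stop inference from past allocations that are visible on the ward.

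**Working it through.** **Inputs from section 2.2.4.** Difference 4 points, SD 8, two-sided alpha 0.025 per main effect ("each tested on a two-sided 2.5% significance level, i.e. 5% with Bonferroni correction for two tests"), power 80%, N 155, then 203, then 250 (50 in each of five countries), ICC 0.01, attrition 20%, blocks of 2 or 4. **Assumption:** equal shares of the two block sizes, since the plan says only "in blocks with sizes of 2 or 4 varying randomly".

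**1. The plan's own sample size.** A two-sample t-test needs 77.3 per arm, or 154.6 in total, which gives 155. With 78 per arm (156) and 156/5 = 31.2 per country, the design effect is 1 + 30.2 x 0.01 = 1.302, and 156 x 1.302 = 203. Allowing for 20% loss, 203/0.8 = 254, against 250 stated. The figures reproduce to within 2%.

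**2. Reading A: one central list per randomization.** Simulation with blocks of 2/4, N = 250 and five countries of 50 in random order gives:
- Overall 1:1 split of each factor: never off by more than 2.
- At least one country at 30:20 or worse: 51% to 52% of trials across runs. At 32:18 or worse: about 17%.
- A site that sees only its own patients and always guesses its lagging arm is right 51% of the time.

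Effect on the estimate: at ICC 0.01 the between-country SD is 8 x sqrt(0.01) = 0.8. Chance country imbalance then adds an SD of 0.09 points to the treatment difference, against a standard error of 8 x sqrt(2/125) = 1.01. At assumed ICCs of 0.05 and 0.10 it adds 0.20 and 0.29.

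**3. Reading B: lists per country or site.** The difference within a country list of 50 is at most 2. For guessing, take one block of each size (six allocations) and an observer who always picks the lagging arm:
- Block of 2: expected correct 1/2 + 1 = 1.5.
- Block of 4: 1/2 + 2/3 + 2/3 + 1 = 2.83.
- Total 4.33/6 = 72%.

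The running count is off by one before 1 + 2 = 3 of the six allocations. The next is then the opposite arm (1 + 2/3 + 1)/3 = 89% of the time.

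For blocks of 4/6, the block of 6 gives 0.5 + 0.6 + 0.6 + 0.7 + 0.7 + 1 = 4.1 correct, so (2.83 + 4.1)/10 = 69%. Given a count off by one, the figure is (1.67 + 2.2)/(2 + 2.9) = 79%. Blocks of 4/6/8 give 68% overall by simulation. If the share of size-2 blocks runs from 25% to 75%, the 72% moves only between 71% and 73%.

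**4. Crossing of the two factors, under either reading.** With n = 250 x 0.8 = 200, the chance correlation between factors has SD 1/sqrt(200) = 0.071 and a 95% limit of 1.96 x 0.071 = 0.14. When both factors are split 1:1, the unadjusted post-discharge comparison carries the NICU effect times this correlation: 4 x 0.139 = 0.55 points at the limit. A model with both factors removes this. At N = 250 the 95th percentile of the correlation is 0.12, a variance inflation of 1/(1 - 0.12²) = 1.015. At N = 155 and a correlation of 0.125, power falls from 80.8% to 80.1%.

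**The case against.** Silence on strata is not proof that none exist, and the concealment arrangement is sound as far as it goes. Both points stand. What the text supports is that the list structure is unstated.

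A reader might go further and infer that the trial is both unbalanced by country and easy to guess. The documents do not support that. Country imbalance needs a central list, which one site can hardly guess; guessability needs an unbroken list visible to the site, which would balance countries. Both could apply only to someone who sees all sites' allocations, or while one site recruits alone, such as the pilot cohort in the recruitment strategy if it draws on the trial list.

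A reader might also infer that half of all blocks have size 2, or that factor balance as a whole is left to chance. The plan gives no shares, and blocking holds each factor's overall split within 2. Only the within-country split and the crossing of factors are open.

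The consequences are small, and the extended model already holds both factors. That is right, but the plan also names an unadjusted t-test or Mann-Whitney for the primary endpoint, and no model has country. Guessing matters less at the second randomization, where participants are already enrolled and timing follows discharge.

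**Conclusion.** The concern holds in limited form. The plan should state its list structure, and each plausible structure has a weakness: chance country splits with central lists, or about 72% guessability with country or site lists. The crossing of the two factors is uncontrolled under both unless the second list is stratified by first arm. The sample size allows for country and the analysis does not.

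The harm is modest. Power falls by under 1 percentage point from the crossing, and country adds about 0.09 points of noise at the plan's ICC. The 0.55-point carry-over is a 95% limit of chance variation, assumes a full 4-point NICU effect, and affects only the unadjusted test. These results rest on equal block-size shares, 50 participants per country in random order for the country splits, and an observer who sees the whole list for the 72%. The point is worth making because the remedy is nearly free, not because the trial is compromised without it.

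**What to change.** - State whether lists are central or per site, and name the stratification factors.
- Stratify the first randomization by country, and the second by country and first arm (5 x 2 = 10 lists, about 25 participants each before losses).
- Replace blocks of 2 with larger random sizes, such as 4 and 6, or 4, 6 and 8, and keep the sizes from the sites.
- Make a model with country and both factors the primary analysis in place of the unadjusted t-test or Mann-Whitney, and include country in all models.

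With blocks of 4 and 6 and no loss before discharge, the largest within-country difference at the first step is 2. The four cells run from about 59 to 66, against 54 to 71 with two independent unstratified lists (2.5th percentile of the smallest cell, 97.5th of the largest).

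The cost is reconfiguring the online lists and revising the analysis text. There are two downsides. Unfinished blocks can leave an imbalance of a few infants. If the list was central, stratifying by country raises guessability within a country from about 51% to 68% or 69% even with the larger blocks. That is why size 2 should go in the same change.

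### Holm's procedure would keep the 5% family-wise error and never be less powerful than the planned Bonferroni rule; per-effect power rises from 80% to about 86% if both main effects are 4 points

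*Combined protocol and SAP*

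**What the plan says.** All of the following is in section 2.2.4 of the combined protocol and SAP.

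- **Planning assumptions:** "Assuming a difference of 4 points on the PBQ ( $SD = 8$ ) as a minimal clinically important difference for this study".
- **Power and level:** "power of 80% will be achieved for each main effect", with the effects "each tested on a two-sided 2.5% significance level, i.e. 5% with Bonferroni correction for two tests", and this is reached "with a sample size of 155".
- **Inflation:** "Taking into account some clustering by country (ICC 0.01; 5 countries), this is increased to 203". Then: "To allow for 20% attrition, we will aim to include 250 infants".
- **Allocation:** the first randomization is "with ratio 1:1, in blocks with sizes of 2 or 4 varying randomly". For the second, "participants will be randomized a second time to post-discharge MT or standard care in a 1:1 ratio".

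Bonferroni is named only in the sample-size paragraph. The data-analysis text that follows names no multiplicity procedure. Section 2.2.3 sets one primary time point for the PBQ, 6 months corrected age, so the p-values for both main effects become available together.

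**The concern.** Under the planned rule each main effect is held to 2.5% even after the other has been declared significant. Holm tests the smaller p-value at 2.5% and, if that passes, the larger at 5%. Its first step is the Bonferroni test, so nothing is lost. The second step can only add rejections. Strong control of the 5% family-wise error holds under any dependence between the two tests.

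What is at stake is power for whichever effect has the larger p-value. A trial with p = 0.01 for one phase of music therapy and p = 0.04 for the other would claim one effect under the planned rule and both under Holm, at the same family-wise error rate.

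**Working it through.** **Inputs (section 2.2.4):** difference 4, SD 8 (standardised difference 0.5), two-sided 2.5% per effect, power 80%, total 155, 1:1 allocation at both randomizations. **Assumption:** the two tests are independent, as is nearly so in a balanced crossed 2x2 design, and both use the same N.

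**1. The plan's figure reproduces.** By the normal approximation, n per level = 2 × (2.241 + 0.842)² × (8/4)² = 76.04, rounded up to 77, or 154 in total. By the noncentral t at N = 155 (noncentrality 0.5 × √155 / 2 = 3.112, 153 df), power is 0.801 at 2.5% (critical value 2.264) and 0.871 at 5% (critical value 1.976). The stated 155 is right.

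**2. Holm when both effects are 4 points.** Write A = 0.8011 for power at 2.5% and B = 0.8714 for power at 5%.

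- Per effect: A + (B − A) × A = 0.8011 + 0.0703 × 0.8011 = 0.857, against 0.801.
- Both effects: A² + 2A(B − A) = 0.642 + 0.113 = 0.754, against 0.642.
- At least one effect: 1 − (1 − A)² = 0.960 under either rule, because the first steps are identical.

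**3. Holm when the effects differ.** Let a and b be the power for the other effect at 2.5% and 5%. Holm power for the 4-point effect is A + (B − A)a. For the other effect it is a + (b − a)A. For both it is Aa + A(b − a) + (B − A)a. At N = 155:

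| Other effect (points) | 4-point effect, Bonferroni → Holm | Other effect, Bonferroni → Holm | Both, Bonferroni → Holm |
|---|---|---|---|
| 0 | 80.1% → 80.3% | (null; see step 4) | not applicable |
| 1 | 80.1% → 80.6% | 7.2% → 11.1% | 5.8% → 10.2% |
| 2 | 80.1% → 81.8% | 24.3% → 32.0% | 19.4% → 28.9% |
| 3 | 80.1% → 83.8% | 52.9% → 61.8% | 42.4% → 55.0% |
| 4 | 80.1% → 85.7% | 80.1% → 85.7% | 64.2% → 75.4% |

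The stronger effect gains little when the other is small. The weaker effect gains more, because the stronger one usually passes first. If both effects are only 2 points, power per effect moves from 24.3% to 0.2427 + 0.0972 × 0.2427 = 26.6%.

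**4. Type I error.** With one true 4-point effect, the error on the null effect is 0.025 + 0.025 × 0.801 = 4.5%. With both effects null, the family-wise error in 400,000 simulated trials was 4.95%. Both are within 5%.

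**5. What the recruited sample is worth.** 250 less 20% attrition leaves 200 analysed. Taken at face value, 200 gives 89.8% (Bonferroni) and 93.6% (Holm) per effect, and 80.7% and 88.3% for both. Those figures ignore clustering. The plan inflates 155 to 203 for it, a factor of 203/155 = 1.31, so 200 analysed is worth about 200/1.31 = 153 independent participants. On the plan's own terms per-effect power is then 79.5% with Bonferroni and 85.2% with Holm, close to the row at 155.

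**The case against.** **Bonferroni is valid, and choosing between valid procedures is partly taste.** This stands. The planned rule controls the error and the sample size follows from it. A reader might infer from Holm's advantage that the plan contains a mistake; the documents do not support that.

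**The gain depends on the scenario.** This stands too. A reader might take 86% as the power Holm delivers in general, but it needs both true effects to be 4 points. Of the five PBQ effects that section 2.2.4 cites from other interventions, four are 2 points or less (0.25, 0.5, 1.4 and 2; the fifth is 9). If the other effect were 2 points or less, a 4-point effect would have at most 81.8% power. Against this, the same spread makes unequal effects plausible, and there the weaker effect gains most.

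**Bonferroni has matching simultaneous 97.5% intervals.** This is a real advantage. Every additional Holm rejection has a p-value between 2.5% and 5%, so with a t-test the simple 97.5% interval includes zero in all of them. Holm is free in type I error and sample size, but not in how simply results can be reported.

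**The plan sets no joint-success criterion.** The primary objective mentions both care phases, and a reader might infer that the trial must show benefit in both. Section 1 speaks of one phase and/or the other, and section 2.2.4 powers each main effect separately. The move from 64% to 75% therefore describes a useful outcome, not a stated goal.

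**Holm cannot simply be dropped in.** It needs one p-value per main effect. The data-analysis text offers a t-test or a Mann-Whitney test, then mixed models in two steps, the first with only the first randomization, then both linear and simple time contrasts. This is right, but Bonferroni needs the same decision.

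**Conclusion.** The point holds as a cheap, optional improvement. Holm is never less powerful than the planned rule at the same 5% family-wise error. Under the plan's own assumptions for both effects, it adds 5.6 percentage points per effect and about 11 points for showing both. The per-effect gain for a 4-point effect falls to about 0.2 points if the other effect is null, and there is no gain in the chance of at least one finding.

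Holm's dominance does not depend on any trial assumption. The percentages rest on 4 points, SD 8, 155 effective participants, independent tests and equal N for both effects; losses between the two randomizations would lower them slightly. The figures of 90% and 94% at 200 analysed should not be quoted without saying that they ignore clustering by country.

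**What to change.** Add to the data-analysis text of section 2.2.4, before unblinding:

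*The two main effects on the PBQ at 6 months corrected age are tested with the Holm procedure at a two-sided family-wise 5% level: the smaller p-value against 2.5% and, if significant, the larger against 5%. Each effect contributes one p-value, taken from [the named primary analysis]. Holm decides significance. The 97.5% confidence intervals are reported as conservative simultaneous intervals, and the interval for the second effect will include zero when its p-value lies between 2.5% and 5%.*

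Keep 2.5% in the sample-size calculation as the conservative planning level, so that the target of 250 does not change. The cost is a short text change, the choice of one primary analysis per effect (needed under either rule), and the reporting mismatch that the added text discloses.

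### The two-group test named for the 6-month PBQ endpoint leaves the other randomized factor in the error term; making a two-factor analysis the deciding test gains up to about 2.7 points of power at N = 155.

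*Combined protocol and SAP*

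**What the plan says.** All of this is in section 2.2.4 of the combined protocol and SAP.

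- **Sample size.** The target effect is introduced by "Assuming a difference of 4 points on the PBQ", and the SD is taken as 8. The claim is that "power of 80% will be achieved for each main effect". The error rate is given as "each tested on a two-sided 2.5% significance level, i.e. 5% with Bonferroni correction for two tests". The total before inflation is 155; allowances for clustering and attrition then raise it to 203 and 250.
- **Randomization.** The first is "with ratio 1:1, in blocks with sizes of 2 or 4 varying randomly". The second, one day before discharge, is also 1:1 by the same procedures. Stratifying it by the first allocation is not mentioned.
- **Endpoint test.** "Effects will be examined by testing the randomized groups for differences in the primary endpoint (t-test or Mann-Whitney; change in PBQ scores". The time point is 6 months corrected age, and the same sentence adds linear mixed models alongside.
- **First model.** "In the first modeling step we will assess the effect of the first randomization". It has time, one group term and their interaction.
- **Second model.** A refinement holds both randomized groups, each with a time interaction. Linear contrasts, and simple contrasts of each visit against baseline, are both to be examined.

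The section does not say which of these analyses decides the two main-effect hypotheses. It also does not say whether SD 8 is the spread within one of the four cells or the spread across both levels of the other factor.

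**The concern.** The sample size is set for two main effects, each tested at 2.5%. A t-test or Mann-Whitney on one factor pools the two levels of the other. If the other phase shifts the PBQ, that shift is counted as noise, although the trial itself created it and knows exactly who received it. The first mixed model has the same feature. A team could follow the plan to the letter and report the less efficient test as primary in the very scenario the trial hopes for, in which both phases work. It could also choose among the listed analyses after seeing the results.

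**Working it through.** **Inputs** (section 2.2.4): difference 4; SD 8; two-sided alpha 0.025 per main effect; N = 155; 1:1 on each factor. Assumed, because the plan is silent: the other factor's effect d2 (range 0 to 4), and whether SD 8 is within cell or total. Effects are taken as additive.

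**1. The plan's own figure.** With an equal split, the noncentrality is 4 / (SD × √(4/N)). At SD 8 and N = 155 this is 4 / 1.285 = 3.11, against a critical t of 2.264 on 153 df. Power is 80.1%. The normal approximation gives 77 per arm, 154 in total. The stated 80% at 155 is reproduced.

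**2. SD 8 within cell, other factor left in the error.** A 1:1 factor with effect d2 adds (d2/2)² to the variance. For d2 = 4 the SD is √(64 + 4) = 8.25, the noncentrality is 3.02 and power is 77.4%. N = 165 would be needed for 80% (164 falls just short). With both factors in the model, the residual SD is 8 on N − 3 = 152 df and power is 80.1%, so the extra degree of freedom costs essentially nothing.

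**3. SD 8 as the total SD.** The single-factor test keeps 80.1%. The two-factor residual SD is √(64 − 4) = 7.75, the noncentrality is 3.21 and power is 82.8%.

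**4. Range over the other phase's effect, N = 155.**

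| d2 (points) | Within cell: one-factor | Within cell: two-factor | Total SD: one-factor | Total SD: two-factor |
|---|---|---|---|---|
| 0 | 80.1% | 80.1% | 80.1% | 80.1% |
| 1 | 79.9% | 80.1% | 80.1% | 80.3% |
| 2 | 79.4% | 80.1% | 80.1% | 80.8% |
| 3 | 78.6% | 80.1% | 80.1% | 81.6% |
| 4 | 77.4% | 80.1% | 80.1% | 82.8% |

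**5. Simulation at N = 156** (within-cell reading, both effects 4). With the second factor not balanced within the first, power is 77.5% for the one-factor test and 80.1% for the two-factor test. With four exactly equal cells it is 78.6% and 80.6%, so the loss is then about 2 points.

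**6. Chance imbalance is not a further loss.** At N = 155, imbalance of the other factor moves the unadjusted estimate with SD 4 × √(0.25 × 4/155) = 0.32, beside a standard error of 1.285. Combined, √(1.285² + 0.321²) = 1.325, which equals 8.25 × √(4/155). This is the same added variance as in step 2.

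**7. At 200 analysed** (250 less 20%), within-cell reading and d2 = 4, before any allowance for clustering: 87.8% against 89.8%.

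Steps 1 to 4 and 7 apply to a t-test and a linear regression. The power of the mixed-model contrast depends on variance components that the plan does not give.

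**The case against.** The strongest reply is that the plan already contains the remedy. Its second mixed model has both factors, and the simple contrast at 6 months is the change from baseline for each factor adjusted for the other. That stands: a reader might infer that the plan has no two-factor analysis of the 6-month endpoint, and the documents do not support this. What remains is that the model is a refinement, that linear contrasts sit beside the simple ones with no choice made, and that nothing makes it decisive.

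A reader might also infer that the stated 80% is not delivered. That needs SD 8 to be a within-cell value and the other phase to have the full 4 points. The SD's meaning is not stated; 8 lies inside a cited range of 4 to 12. The 4 points are a minimal important difference used for each main effect, not a forecast that both phases reach it. The earlier PBQ effects cited run from about 0.25 to 9.

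The loss is also small beside the uncertainty in the SD: at N = 155 an SD of 9 would already give 69%. This is a fair reason not to treat the point as a serious power failure, but it is no reason to prefer the weaker test.

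Finally, a first step holding only the first randomization has a merit. It keeps in the NICU-MT comparison anyone who never reaches the second randomization, which suits the intention-to-treat rule. A two-factor regression without a coding rule would drop them. This stands, and the fix has to deal with it.

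**Conclusion.** The point holds as a matter of efficiency and of naming the deciding analysis. The test attached directly to the endpoint ignores a known randomized factor, and the two-factor alternative is present but not made decisive. The gain from using it is at most about 2.7 points at N = 155 over the range of effects considered (0 to 4 points). On the within-cell reading of SD 8 it restores the planned 80%; on the total-SD reading it raises power above 80%. It is about 0.7 points if the other phase has a 2-point effect, and nil if it has none. These figures assume additive effects, an equal split on both factors and normal errors. Chance imbalance between the factors should not be cited as bias or as an additional harm.

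**What to change.** 1. Name one two-factor analysis of the 6-month PBQ endpoint as the primary test of each main effect at two-sided 2.5%. It can be a linear regression on both randomized factors, or the 6-month simple contrast from the plan's second mixed model.
2. Make the t-test and Mann-Whitney supportive. If a rank test is wanted, stratify it by the other factor (van Elteren).
3. State how participants who were never re-randomized stay in the NICU-MT comparison. One option is a separate level of the second factor for them. Because reaching the second randomization happens after the first, that level adjusts for a later event. If NICU-MT could affect who reaches it, scoring the second factor −½, +½ and 0 (not re-randomized) keeps these participants without that adjustment.
4. State whether SD 8 is within cell or total.

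The cost is a change of wording, one degree of freedom (two with a separate level) and the coding rule. No design change or extra recruitment is needed.
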